### Assessment procedures

2.4.

Participants will complete four clinic visits (screening/baseline 1 visit, baseline 2 visit, week 8, and week 12) for the study. Two baseline visits are conducted to: (1) minimize the length of clinic visits by collecting surveys and clinical data on two separate dates, and (2) as a way of assessing compliance with study protocols. Participants are provided 24-h urine collection materials and the home BP monitor at the end of the first baseline visit. If they have completed the at-home urine and BP data collection when they return for the second baseline visit, they are considered compliant with study protocols. Compensation will be in the form of gift cards to local gas stations or grocery stores in the following amounts: second baseline visit ($50), 8- and 12-week visits ($50 each).

For the extended support pilot study, telephone interviews will be conducted to collect home BP data using the same study-provided devices at six and 9 months post-baseline. About 5 months post-baseline, pilot study participants will be contacted to schedule the 6-month data collection interview and provide re-training in use of the home BP cuff, if necessary. The 6- and 9-month interviews will be conducted by telephone by research staff who are masked to treatment group assignment. Staff will talk each participant through the process of accessing BP values stored in the cuff’s memory. Participants will read off values, and staff will enter them into a study database. Phone conversations will be recorded as electronic data files and erased after quality control checks have been completed.

### Randomization

2.5.

Treatment conditions will be randomly assigned after the participant completes the clinical data collection at the second baseline visit. The study staff will generate treatment assignments using the randomization function in the study’s REDCap database.

### Intervention

2.6.

The DASH diet is low in saturated fat, cholesterol, and total fat, focuses on fruits, vegetables, and fat-free or low-fat dairy products, and is rich in whole grains, fish, poultry, beans, seeds, and nuts. It minimizes intake of ultra-processed foods, including sweets, added sugars, and sugary beverages, as well as red meats compared to the typical American diet. Its unique composition of prescribed food groups results in a nutrition profile that is lower in sodium and rich in potassium, magnesium, and calcium. The intervention group will receive one in-person, tailored nutrition counseling visit at baseline and weekly 15-min telenutrition sessions in weeks 2–8 to provide additional DASH diet education and behavior change support.

After the final DASH session is complete, a questionnaire will be mailed to the participant in order to evaluate their satisfaction with the program. The 14-item anonymous questionnaire asks participants to rate their degree of agreement with statements such as, “The information about the DASH diet was easy to understand,” “It is difficult for me to do exactly what the nutrition staff recommended,” and “I will be able to follow the DASH diet and nutrition staff’s advice after the program.” Additional questions ask what participants liked about the program, what could have been improved or changed, what activities or information was most useful, and what diet and lifestyle changes were the most difficult to change.

During the extended support pilot study, the 25 intervention participants receiving extended support will continue to receive weekly 15-min phone consultations with the RD for an additional 6 weeks (weeks 9–14) after the end of the original 8-week study period. Consultations will provide support for continuing the DASH diet and will focus on overcoming barriers to obtaining and preparing healthy foods within the context of each person’s regular food budget and resources.

#### In-person nutrition visit

2.6.1.

Following randomization to the intervention group, participants will be scheduled for an initial appointment with an RD employed by the clinic and trained on all study procedures. This 55-min counseling visit will include: purpose of study visit (5 min.), energy needs calculation (5 min.), overview of the DASH diet based on calorie needs (15 min.), basic education on health risks of high BP and interpretation of current BP (4 min.), elicitation of patient perspective on which eating behaviors are affecting BP and ranking of readiness for behavior change (8 min.), co-creation of a customized eating plan (10 min.), and discussion of other lifestyle factors that may be affecting BP (e.g., tobacco use) (8 min.). Following the visit, the RD will assist participants with completing their first grocery order (10 min.). Participants will be provided with a daily eating goal handout for each DASH food group based on their estimated calorie needs. This handout was developed by a study co-investigator and RD ([name]), which was then reviewed and approved by RD community research staff. The handout includes references to hand images for each food group to estimate portion size (e.g., fist, palm, thumb) in addition to standard household measures (e.g., cup, Tablespoon). Participants will also receive a 56-page DASH diet booklet published by the NHLBI (53). During each weekly telephone session with the RD, specific pages of the booklet are referenced to facilitate participants’ gradual review of its content.

#### Weekly telephone RD consultations

2.6.2.

NOSH was developed to provide follow up medical nutrition therapy via telenutrition for the management of HTN. Typically delivered in person over multiple sessions, medical nutrition therapy is an evidence-based approach used by RDs to address chronic conditions, including HTN (54). However, multiple barriers, such as transportation and costs, preclude patients from accessing in-person healthcare, including medical nutrition therapy (55–57). The NOSH telenutrition curriculum will be delivered either over the phone or via password-protected secure Zoom platform, depending on participant preference, across eight weekly sessions by an RD or trained health educator under the direct supervision of an RD. Each session will begin with a check-in discussion about current BP monitoring at home with participant reporting of at-home readings (5 min.), interactive discussion about a particular eating goal within the DASH diet using a scripted, culturally-tailored telenutrition curriculum (10 min.), and placement of a $30 unrestricted grocery order (5 min.). Weekly topics will include: (1) seasoning without sodium; (2) fruits instead of processed sweets; (3) vegetables; (4) nuts, seeds, and beans; (5) whole grains; (6) healthy fats; (7) high-calcium dairy alternatives and low-fat dairy; and (8) lean meat, poultry, and fish. Telenutrition curriculum topics will relate to items that comprise the DASH diet score and include 2–3 learning objectives per session. Each session will incorporate motivational interviewing (58, 59) and provide time for the participant to reflect upon current eating behaviors, rate self-confidence in making needed eating behavior change, and develop a weekly action plan to improve dietary adherence within that session’s topic. This curriculum script for weekly telephone sessions was developed by a study co-investigator and RD ([name]), which was then reviewed, culturally tailored, and approved by RD community research staff. These staff members had various levels of experience that ranged from 7 years working with AI/AN adults to more than 20 years of experience working with AI/AN adults in their specific communities. At the end of each session, the RD will assist participants in placement of an unrestricted grocery order. A weekly list of suggested DASH foods specific to that week’s telenutrition topic was developed by the academic-community nutrition team for RD reference. Weekly food lists emphasized a variety of affordable perishable and non-perishable foods that could be accessed at the local grocery store.

#### Registered dietitian training

2.6.3.

RDs will be trained in patient-centered care and communications skills in three 2-h webinars. Sessions will be conducted by a master trainer who was involved in the DASH trials. Topics will include HTN, how to work with people with limited health literacy/numeracy skills, and how to address barriers to DASH and medication adherence. Webinars also will include a detailed review of the DASH diet and strategies to assess diet, set goals, provide advice, arrange follow-up, and monitor progress. Finally, a didactic session with role-playing will be completed to ensure training comprehension. Fidelity will be maintained through booster sessions conducted every 6 months.

### Control condition

2.7.

NOSH is a wait-list control trial. The control condition will receive a single printed brochure about the health benefits of a low-sodium diet after the second baseline visit, complete weekly phone calls to collect BP readings, and place $30 grocery orders. After all study data collection is complete, participants will be offered the same in-person, hour-long nutritional counseling session with the study RD that was provided to the intervention group, in addition to the eight weekly telenutrition calls without additional grocery credits provided.

### Primary outcome

2.8.

The primary study outcome will be systolic BP assessed at home as the average of three readings spaced 30 s apart using a Microlife 3BTO Plus (60). Participants will be instructed to take their BP at least two times a day (morning and evening) for 7 days before visits at baseline, 8 weeks post-baseline, and 12 weeks post-baseline. During the initial set up of the home BP monitors, measurements will be checked against clinic BP monitor measurements or manual measurements to ensure accuracy of home BP readings. For pilot study participants, home BP monitoring will also be conducted during the 6- and 9-months post-baseline interviews.

### Secondary outcomes

2.9.

#### Blood pressure (clinic visits)

2.9.1.

At the first baseline visit and at every subsequent clinic visit, systolic and diastolic BP will be measured on-site by auscultation using a mercury sphygmomanometer. A total of three BP measurements, separated by 30 s, will be obtained at each visit on the right arm of participants, using a cuff of appropriate size, after they rest quietly in the seated position for at least 5 min. If the participant indicates that there is a medical or post-surgical reason for not having the BP measured on the right arm (or if the right arm is missing), then BP will be measured with the cuff on the left arm.

#### Body composition

2.9.2.

Height and weight will be measured at the second baseline visit to calculate BMI as a continuous variable (kg/m^2^) and categorized to conventional thresholds (< 25 kg/m^2^ = normal; 25–29 kg/m^2^ = overweight; ≥ 30 kg/m^2^ = obese). Weight will be measured and at each following clinic visit to calculate BMI. Participants will be asked to remove shoes, heavier outerwear, and to empty heavy items from their pockets before weighing. If a participant is unable to remove shoes or heavier outerwear, two pounds will be removed from weight.

#### Lipids

2.9.3.

Fingerstick blood samples will be acquired at the second baseline visit and at each follow-up clinic visit to assess blood lipids. Blood lipids will be measured as total cholesterol, HDL cholesterol, LDL cholesterol, and triglycerides (all mg/dL), using the Cholestech portable analyzer (61). Hyperlipidemia will be defined as LDL cholesterol >130 mg/dL.

#### Dietary intake

2.9.4.

Two methods will be used to evaluate dietary intake at the second baseline visit and at each of the follow-up clinic visits. First, at the baseline, 8-, and 12-week assessments, the site study coordinator will assist participants with completing a food recall using the Automated Self-Administered 24-Hour (ASA24®) Dietary Assessment Tool developed by the National Cancer Institute (62). This website guides participants through a 24-h food recall and provides an animated guide and audio and visual cues that enhance use in low-literacy populations. Respondents report frequency of eating occasions and times of consumption. Detailed prompts assess food preparation, portion size, food source, and additions to food items. Dietary intake estimated through the ASA24 will be used the primary method for estimating changes in dietary intake for various components of the DASH diet across study timepoints and between intervention groups. Second, at baseline, self-reported consumption of fats, fruits, and vegetables will be assessed using the validated Block Food Frequency Questionnaire, which reflects dietary patterns during the past year (63). To reduce respondent burden at 8- and 12-week assessments, participants will complete the Fruit and Vegetable Screener, a validated, self-report measure of daily fruit and vegetable intake (64) and the Fat Screener, a questionnaire which assesses percent of energy intake from fat (65). Respondents are asked to indicate how often during the prior month they ate a variety of fruits and vegetables and a variety of food products that are high in fat, respectively. The (65) These food frequency questionnaires will be used to descriptively characterize any dietary changes indicated by the ASA24.

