### Data analysis

2.12.

All data collected on-site will be scanned and uploaded to a secure server and entered into a REDCap database (72). Data will be reviewed by the biostatistician monthly to quickly identify data quality issues. For quality control, data from 10% of randomly selected participants will be entered twice. An intention-to-treat analysis will be used. Success of randomization will be assessed by using t-tests and chi-squared tests to compare baseline variables in the intervention and control groups. All inferential results will be presented as point estimates with 95% confidence intervals. Data analysis will be performed using Stata 14 (StataCorp LP, College Station TX, 2013).

Linear regression will be used to compare primary and secondary outcomes between the intervention and control groups at 8- or 12-week post-baseline assessments, with treatment group, baseline value, and study site as the independent variables. Since there may be differences between the study sites regarding availability of healthy food at local stores, an interaction term between intervention and site will be included. If the interaction is significant, all analyzes will be repeated after stratifying by site. Sensitivity analyzes will adjust for variables that appear unbalanced between groups at baseline. All 370 participants will be included in the analysis of data from the 8-week visit, but the 25 pilot study extended support (intervention group) participants will be excluded from analyzes involving data from the 12-week visit. Next, generalized estimating equations will be used to simultaneously assess outcome values measured at 8 and 12 weeks. To assess effectiveness of the extended support pilot study, a generalized estimating equation will be used to analyze data for all four time points (8 weeks, 12 weeks, 6 months, and 12 months), with independent indicators for each time point that do not impose a linear trend on the outcome. These models adjust standard error estimates to properly account for within-person correlation in the outcome values over time.

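### Change from baseline on the diet questionnaires cannot be separated from the switch from a past-year questionnaire to past-month screeners

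*Protocol article*

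**What the plan says.** All the relevant text on measurement is in section 2.9.4, Dietary intake, of the Protocol article.

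- The section opens: "Two methods will be used to evaluate dietary intake at the second baseline visit and at each of the follow-up clinic visits".
- The first method is the ASA24 recall, given at baseline and at 8 and 12 weeks. It is the "primary method for estimating changes in dietary intake for various components of the DASH diet across study timepoints and between intervention groups".
- The second method is by questionnaire. At baseline it is the "validated Block Food Frequency Questionnaire, which reflects dietary patterns during the past year".
- At follow-up the instrument changes: "To reduce respondent burden at 8- and 12-week assessments, participants will complete the Fruit and Vegetable Screener", together with the Fat Screener. The recall window changes too: "Respondents are asked to indicate how often during the prior month they ate a variety of fruits and vegetables", and likewise for high-fat foods.
- The purpose is then stated: the questionnaires "will be used to descriptively characterize any dietary changes indicated by the ASA24".

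The section does not schedule the screeners at baseline or the Block questionnaire at follow-up. It describes no calibration between them.

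**The concern.** Describing change needs the same measure before and after. Here the before measure is one instrument with a 12-month window, and the after measure is a different pair of instruments with a one-month window. A difference between them contains true dietary change, any difference in level or scale between the instruments, and the difference in recall window, which also brings in season.

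The risk is a misleading before-and-after statement about diet. Both arms could appear to improve or worsen when neither has, or a real improvement in the intervention arm could disappear. The questionnaires are there to fill out the ASA24 picture of change. On change from baseline they could appear to support or contradict the ASA24 for reasons unrelated to diet.

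A later analysis plan cannot repair this, because a baseline screener score that was never collected cannot be recovered.

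**Working it through.** The article gives no figure for this point, so there is none to reproduce. The check sets the schedule out by visit and then asks what a change score would contain.

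**Step 1. Instruments by visit (section 2.9.4).**

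| Measure | Baseline | Week 8 | Week 12 | Same tool throughout? |
|---|---|---|---|---|
| ASA24 | 24-hour recall | 24-hour recall | 24-hour recall | Yes |
| Fruit and vegetable questionnaire | Block, past year | Screener, prior month | Screener, prior month | No |
| Fat questionnaire | Block, past year | Screener, prior month | Screener, prior month | No |

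**Step 2. What a change score contains.** Let mean true baseline intake be μ and true change be Δ. Suppose the follow-up instrument reads at offset *a* and scale *s* relative to the baseline instrument. Then

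- apparent mean change in an arm = a + s(μ + Δ) − μ = a + (s − 1)μ + sΔ
- between-arm difference at follow-up = s(Δ_int − Δ_ctrl)

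The offset enters within-arm change in full and cancels between arms, provided the instruments behave alike in both arms.

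**Step 3. Illustration.** All values are assumed: μ = 4 units, Δ = 0 in control and +1 in intervention, offset −1, 0 or +1, scale 1.0 or 0.7.

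| a | s | Control: a + (s − 1)4 | Intervention: control + s | Difference between arms |
|---|---|---|---|---|
| −1 | 1.0 | −1.0 | 0.0 | 1.0 |
| 0 | 1.0 | 0.0 | 1.0 | 1.0 |
| +1 | 1.0 | +1.0 | 2.0 | 1.0 |
| −1 | 0.7 | −2.2 | −1.5 | 0.7 |
| 0 | 0.7 | −1.2 | −0.5 | 0.7 |
| +1 | 0.7 | −0.2 | +0.5 | 0.7 |

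The true control change is zero in every row, yet the apparent change runs from −2.2 to +1.0. In the first row the intervention arm's real gain of one unit vanishes. The between-arm difference does not depend on the offset. At scale 0.7 it is 0.7 only because it is expressed in the follow-up instrument's units. A simulation with these values (baseline SD 1.5, error SD 1 on each instrument, 200,000 participants per scenario) agreed. The baseline-adjusted between-arm estimate was 0.99 to 1.00 at scale 1.0 and 0.69 to 0.71 at scale 0.7.

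**Step 4. Would repeating the Block questionnaire be the answer?** At week 8 a past-year window holds 8/52 = 15% post-baseline time, and at week 12 it holds 12/52 = 23%. Most of the window would describe diet before the intervention. A short window at follow-up is therefore sensible, and the gap is the missing short-window measure at baseline.

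**The case against.** The strongest reply is that the article never says screener scores will be subtracted from Block scores. The ASA24 identifies the change and the questionnaires only describe it. Valid descriptive uses remain: comparing arms at weeks 8 and 12, and screener change from week 8 to week 12. The switch has a stated reason, respondent burden, and section 2.4 (Assessment procedures) explains that baseline was split over two visits to keep each one short. The article is also a condensed account, and scoring and tabulation may be set out elsewhere.

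Much of this stands. The valid uses are real, and Step 4 supports the short window at follow-up. But the sentence on purpose covers the questionnaires together and names dietary changes as their object. The change of most interest, from baseline to the end of the 8-week intervention, is the one they cannot show. Burden explains dropping a long questionnaire at follow-up. It does not explain leaving two short screeners out of baseline. Which instrument is given at which visit is a matter of data collection, not tabulation. If the full protocol does schedule the screeners at baseline, the point reduces to correcting the article.

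Three stronger readings are tempting, and the article does not support them.

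- *The questionnaires are the only check on the ASA24.* They are not. Section 2.9.5 measures sodium and potassium in urine by one method at the second baseline visit and each follow-up visit. Urine says nothing about fat intake, but it is an objective check on other parts of the diet.
- *The outcome regression lacks a valid baseline for these scores.* Section 2.12 (Data analysis) does model secondary outcomes "with treatment group, baseline value, and study site as the independent variables". However, section 2.9.4 gives the questionnaires a descriptive role, and nothing clearly places screener scores in that model. A baseline covariate from a different instrument would still leave the randomised comparison valid.
- *A definite loss of precision follows.* Any figure would need correlations between the instruments, which the article does not give.

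**Conclusion.** The point holds in a limited form. On the schedule as published, change from baseline in questionnaire-reported fat, fruit and vegetable intake is confounded with the change of instrument and recall window. The size of the error is unknown. The figures in the illustration show the mechanism and are not estimates for this trial.

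The switch of questionnaire leaves the following untouched:

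- home systolic blood pressure, the primary outcome
- the ASA24, the primary dietary measure
- the urinary electrolytes
- between-arm comparisons of the screeners at weeks 8 and 12, because both arms switch together
- screener change from week 8 to week 12

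Because the questionnaires are a descriptive supplement, this is a minor, worthwhile correction and not a threat to the trial's conclusions. It rests on reading section 2.9.4 as the complete questionnaire schedule.

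**What to change.** **Preferred.** Give the Fruit and Vegetable Screener and the Fat Screener at the second baseline visit as well, and describe change on the screeners only. The Block questionnaire can stay as a description of usual diet at entry. The cost is a small added burden at a visit already scheduled. This removes the mismatch of instrument and recall window. It does not remove season from within-arm change, since baseline and follow-up still fall 8 to 12 weeks apart, so the comparison between arms should be shown beside it.

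**If baseline cannot be changed.** Reword the sentence on purpose in section 2.9.4. The screeners would be compared between arms at weeks 8 and 12 only, optionally with baseline Block scores as a covariate, and no change from baseline would be reported on these instruments. This costs wording only, but gives up any questionnaire-based description of change from baseline.
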